### Recruitment {15}

It is intended to randomise 134 patients in approximately 10 centres within 36 months. There is no limit to the number of included patients at an individual study site. Patients with the first single decompensating event with ascites are also often seen in local hospitals and are allocated to a tertiary medical centre mostly only if ascites cannot be controlled after several LVPs and extensive diuretic treatment. In order to fulfil preliminary assumptions on recruitment rates, specific strategies (continuous medical education [CME] events to present the study to local family doctors, out-patient gastroenterologists and local hospitals, providing information material [flyer, presentation]) will be prepared.

## Assignment of interventions: allocation

### Sequence generation {16a}

If the informed consent is obtained, the qualified/authorised personnel will register the patient online in the eCRF (REDCap® system) by creation of a new patient record. The system will automatically assign the next consecutive number (e.g. 1, 2, 3). The unique patient identification number will then consist of a unique centre number assigned by REDCap® combined with the consecutive patient number. The registration date, the date on which the first patient data is entered in the eCRF, will be automatically collected.

The randomisation list will be provided by the biometrician and will be uploaded into REDCap®. The randomisation itself will be performed at the study site on the electronic randomisation form in REDCap®. The randomisation can only be performed if all requirements for randomisation are fulfilled (i.e. eligibility criteria of the patient for randomisation must be confirmed). The randomisation process is started by pushing the “randomise” button in the randomisation form. The randomisation result will be displayed in the form and is saved automatically. A notification of the randomisation result will be sent automatically via E-mail to the responsible data manager of the Clinical Trials Unit (CTU), and the principal investigator at the specific site.

Randomisation will be performed, stratified by site, in blocks of variable length in a ratio of 1:1. The block lengths will be documented separately and will not be disclosed to the sites. The randomisation code will be produced by validated programmes based on the Statistical Analysis System (SAS).

### Concealment mechanism {16b}

The randomisation is done via eCRF (REDCap® system) (see the Sequence generation {16a} section), which permits concealment of the randomisation sequence.

### Implementation {16c}

The randomisation code will be generated by the CTU to ensure that treatment assignment is unbiased and concealed from patients and investigator staff.

## Assignment of interventions: blinding

### Who will be blinded {17a}

Blinding is not possible due to the interventional character of the study.

### Procedure for unblinding if needed {17b}

This is not applicable as the study is designed as an open-label trial.

## Data collection and management

### Plans for assessment and collection of outcomes {18a}

Examinations and assessments will be performed at pre-defined timepoints as specified in Table 2. Data will be entered by the investigator/authorised personnel in the eCRF (REDCap® system). Questionnaires (SF-36 and CLDQ) are first filled out on paper and then transferred to the eCRF. At each visit, patient life status, liver transplantation and paracentesis performed are queried. Events related to TIPS implantation during and after the end of the procedure, categorised incidences for all patients and all other adverse events are collected in a patient safety form in the eCRF.

### Plans to promote participant retention and complete follow-up {18b}

In the first year after randomisation, regular and timely visits support patient contact. After the first year, phone calls also promote long-term follow-up.

### Data management {19}

The setup of the eCRF and data management will be performed with the REDCap® system.

REDCap® uses built-in security features to prevent unauthorised access to patient data, including an encrypted transport protocol for data transmission from the participating sites to the study database. An audit trail provides a history of the data entered, changed, or deleted, indicating the processor and date.

Before any data entry is performed, the trial eCRF will be validated. Site data entry personnel will not be given access to the trial database until they have been trained.

Data will be checked during data entry by programmed warnings and so-called data rules. Furthermore, the Query Module of REDCap® will be used to assign queries manually and control data quality by executing data quality rules. Data corrections will be entered directly into REDCap® by the responsible personnel.

Furthermore, the data will be reviewed for completeness, consistency, plausibility and regarding protocol violations or distinctive medical problems using SAS® software. The resulting queries will be sent to the investigators for correction or verification of the documented data in the eCRF.

### Confidentiality {27}

The investigator must ensure anonymity of the patients; patients must not be identified by names in any documents submitted to the sponsor. Signed informed consent forms and patient enrolment log must be kept strictly confidential to enable patient identification at the site. All study-related information will be stored securely at the study site. All participant information will be stored in locked file cabinets in areas with limited access. All laboratory specimens, reports, data collection, processes and administrative forms will be identified by a coded identification number only to maintain participant confidentiality.

### Plans for collection, laboratory evaluation and storage of biological specimens for genetic or molecular analysis in this trial/future use {33}

Blood and urine samples will be collected at pre-defined timepoints as specified in Table 3. These data are collected in order to assess the safety and efficacy of the therapy in each group. Storage of biospecimens for further research is not planned. Embedded future substudies using data from the eTIPS study must have a specific protocol and must be confirmed by the coordinating investigator. Further, a specific approval from the ethics committee is obtained separately.

## Statistical methods

### Statistical methods for primary and secondary outcomes {20a}

The following populations for analyses are defined: (I) The population targeted by the primary estimand will be called full analysis set (FAS). This means that the patients will be analysed in the treatment arms to which they were randomised. All randomised patients will be included in the FAS. (II) The safety set (SAF) includes all randomised patients who underwent TIPS procedure or received SMT, and patients are analysed according to the received treatment.

The estimand and competing events are described above and summarised in Table 4.

**Table 4 Tab4:** Estimand and competing events

(Intercurrent) events	Time to	
	**Transplantation free survival**	**Ascites with need for paracenteses**
**Transplantation**	Event	Competing
**Ascites with need for paracenteses**	Ignore	Event
**Death**	Event	Competing
**TIPS implantation**	Ignore	Not available/event
**TIPS revision**	Ignore	Not available/event

The effects of SMT and TIPS implantation with respect to the primary endpoint transplantation-free survival will be estimated and tested by Cox regression. The regression model will include treatment and study site as independent variables, as well as baseline bilirubin, creatinine and age. As an estimate of the effect size, the hazard ratio between the two treatment arms will be given with the corresponding asymptotic two-sided 95% confidence interval. The two-sided test on the difference between SMT and TIPS at significance level 5% will be based on the corresponding asymptotic two-sided 95% confidence interval from the Cox regression model.

The effects of SMT and TIPS implantation with respect to the secondary endpoint time to ascites with need for paracenteses will be estimated and tested by Cox regression. The probability of event over time will be estimated by cumulative incidence rates due to competing events, transplantation and death. The time to event will be compared between the treatment groups with Cox regression models for the event-specific hazard functions using two-sided Wald tests. The regression model will include treatment and study site as independent variables, as well as baseline bilirubin, creatinine and age. As an estimate of the effect size, the event-specific hazard ratio between the two treatment arms will be given with the corresponding asymptotic two-sided 95% confidence interval.

SF-36 and CLDQ will be compared between treatment arms at two different timepoints (months 6, 12). At both timepoints, a mixed linear model for repeated measures (MMRM) is used modelling the respective scale at this and the earlier timepoints, and including randomised treatment and the baseline value of the respective subscale and centre as covariates. Two-sided *p* values of the tests of the hypotheses that the treatment effect is zero at the respective timepoints will be calculated from these models. As estimates of the effect sizes, the differences of adjusted means (TIPS arm vs.SMT arm) will be calculated with two-sided 95% CI.

The total number of AEs, the minimum, maximum and mean number of adverse events (AEs) per patient, the total number of follow-up (FU) days (number of days in the observation period), the number of AEs per FU-day (total number of AEs divided by the total by the number of follow-up days), the number of patients who had at least one AE and the number of patients who stopped treatment due to AE will be given.

The probability of AEs defined by preferred term (PT) according to MedDRA and of AEs defined by system organ class (SOC) according to MedDRA will be estimated by the Aalen-Johansen estimator. For this purpose, the time from randomisation to the first occurrence of the specific type of AE (defined by PT or defined by SOC) will be analysed. For patients not experiencing the specific type of AE, the time to the end of the documentation period or death, whatever occurs first, will enter the analysis and will be treated as a competing event. This will result in probability estimates (cumulative incidences) for the different AE types (defined by PT and by SOC) over time. The results will be displayed in summary tables by showing the cumulative incidences at the maximum observation time. Incidences of AEs will be calculated with 95% confidence intervals. Additionally, the number of non-serious AEs will be summarised by PT and by SOC.

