### Criteria for discontinuing or modifying allocated interventions {11b}

Patients in the SMT group may be allocated to TIPS implantation according to current Baveno VII guidelines and the EASL guideline for the management of decompensated cirrhosis [1, 5, 7, 21]. TIPS implantation is indicated in the following situations:Massive variceal bleeding with implantation of a fully covered self-expanding metal stent (fcSEMS) for bleeding control (rescue TIPS implantation) [22].Variceal bleeding (esophageal or gastric varices) in patients with Child–Pugh B > 7 points and active bleeding during index gastroscopy or patients with Child–Pugh C < 14 points (pre-emptive TIPS implantation) [7].Recurrent esophageal bleeding in patients with Child–Pugh A or Child–Pugh B 7 points despite adequate secondary prophylaxis with beta-blockers and endoscopic band ligation (EBL) [7].Recurrent ascites (as defined by requirement of ≥ 3 large-volume paracenteses [removal of > 5 L of ascites] within 1 year) in stable situations can be considered for TIPS implantation. Importantly, only paracenteses in stable conditions will be considered. Stable conditions are defined as a clinical situation without concomitant infections, without acute kidney injury and/or bleeding at the time of paracentesis [1, 7].

If TIPS implantation is planned in the SMT arm, the indication should be discussed with the coordinating investigator.

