*Variable (endpoint):* The endpoint is transplantation-free survival defined as time from randomisation to liver transplantation or death.

*Intercurrent events*: ascites, TIPS implantation and TIPS revision will be ignored.

*Population-level summary:* The population-level summary is defined by the statistical analysis approach.

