### Definition of the secondary estimands

#### Estimand 2

Estimand 2 that corresponds to the secondary trial objective to assess the efficacy of TIPS implantation on the course of liver disease is specified by the following 5 attributes. *Population: [A], Treatments: [A].*

*Variable (endpoint):* The endpoint is ascites with need for paracenteses defined as time from randomisation to date of paracentesis.

*Intercurrent events*: transplantation, death will be considered as competing events.

*Population-level summary:* The population-level summary is defined by the statistical analysis approach which is described below.

#### Estimand 3

Estimand 3 that corresponds to the secondary trial objective quality of life is specified by the following 5 attributes.

*Population [B,C]:* 6, 12-month survival of FAS *Treatments:* [A].

*Variable (endpoint):* The endpoint is quality of life measured by SF-36 and CLDQ.

*Intercurrent events:* There are no intercurrent events not already addressed by the specification of population, treatments and variables.

*Population-level summary:* The population-level summary is defined by the statistical analysis approach which is described below.

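### Table 4 gives TIPS implantation and TIPS revision an undefined entry for time to paracentesis that conflicts with Estimand 2, so the secondary hazard ratio depends on how the cell is read

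*Protocol article*

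**What the plan says.** Estimand 2 in the protocol article (Definition of the secondary estimands) states: "The endpoint is ascites with need for paracenteses defined as time from randomisation to date of paracentesis". Its intercurrent-event line reads "transplantation, death will be considered as competing events" and does not mention TIPS implantation or revision.

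The analysis text in {20a} agrees: "The probability of event over time will be estimated by cumulative incidence rates due to competing events, transplantation and death". The effect measure comes from a Cox model: "the event-specific hazard ratio between the two treatment arms will be given with the corresponding asymptotic two-sided 95% confidence interval", with a two-sided Wald test.

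Table 4 in the same section is introduced with "The estimand and competing events are described above and summarised in Table 4". In its paracentesis column, transplantation and death are competing and ascites needing paracentesis is the event. The two remaining rows, TIPS implantation and TIPS revision, both read "Not available/event". No footnote or text explains the entry.

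For the primary endpoint, text and table agree. Estimand 1 says "ascites, TIPS implantation and TIPS revision will be ignored", and Table 4 has *Ignore* in the corresponding cells.

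**The concern.** A table that summarises the estimands should not contain a rule that the estimands lack. A programmer working from Estimand 2 would count only paracenteses. One working from Table 4 could also count a TIPS implantation or a revision as the endpoint. These are two different endpoints, and this one is formally tested.

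The extra events would not fall evenly across the arms. Under {11b}, "Patients in the SMT group may be allocated to TIPS implantation according to current Baveno VII guidelines", and three of the four listed indications concern variceal bleeding, so an SMT patient can receive TIPS without an earlier paracentesis. Revision needs a shunt, so it would add events mainly in the TIPS arm. Table 3 places the randomised TIPS on day 1–7 after randomisation, inside the time-to-event window, and Table 4 does not exclude it. In an open-label trial, the choice should not be left until outcome data can be seen.

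**Working it through.** **Plan's own figure.** The article gives no design figure for this endpoint. The only one to reproduce is the 57 primary events. With HR = ln(0.82)/ln(0.66) = 0.4776, two-sided 5%, 80% power and 1:1 allocation, the Schoenfeld formula gives 4 × (1.960 + 0.842)² / (ln 0.4776)² = 57.49, close to the stated 57. TIPS is ignored for that endpoint in both text and table, so nothing below touches it.

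**Text and table side by side (time to paracentesis).**

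| Occurrence | Estimand 2 and {20a} text | Table 4 |
|---|---|---|
| Paracentesis | event | event |
| Transplantation, death | competing | competing |
| TIPS implantation | not named | "Not available/event" |
| TIPS revision | not named | "Not available/event" |

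Only the two TIPS rows disagree.

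**Effect on the hazard ratio.** All rates here are assumptions, taken as constant hazards per year:
- first paracentesis: 0.90 in SMT, 0.36 in TIPS;
- *s*, TIPS before any paracentesis in SMT: 0.02 to 0.10;
- *r*, revision before any paracentesis in the TIPS arm: 0.05 to 0.20.

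Counting an occurrence as an event adds its hazard to that arm:

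| Rule | Formula | Hazard ratio |
|---|---|---|
| Paracentesis only (Estimand 2) | 0.36 / 0.90 | 0.40 |
| Plus TIPS in SMT | 0.36 / (0.90 + *s*) | 0.39 (*s* = 0.02) to 0.36 (*s* = 0.10) |
| Plus revision | (0.36 + *r*) / 0.90 | 0.46 (*r* = 0.05) to 0.62 (*r* = 0.20) |
| Plus both | (0.36 + *r*) / (0.90 + *s*) | 0.41 (*r* = 0.05, *s* = 0.10) to 0.61 (*r* = 0.20, *s* = 0.02) |

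The two additions cancel when (0.36 + *r*) / (0.90 + *s*) = 0.40, that is when *r* = 0.40 × *s*. With *s* = 0.10 this is *r* = 0.04, just below the assumed range.

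**Index TIPS.** If the randomised procedure also counted, nearly every TIPS-arm patient would have an event by about day 7. In SMT, at 0.90 per year, the proportion with an event by then would be 1 − exp(−0.90 × 7/365) = 1.7%. The hazard ratio would reverse to far above 1. Simulated Cox fits for this case did not converge reliably, so no value is given.

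**The case against.** The strongest reply is that the cell does not plainly say *event*. It may be meant by arm: implantation is not available as an intercurrent event in the TIPS arm, where it is the assigned treatment, and is an event in SMT; for revision the arms are the other way round. That is a sensible reading and would remove the index TIPS. But the article does not state it, and it still leaves two kinds of event that Estimand 2 does not contain.

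Three further points limit the concern, and they stand:
- A reader might infer that revisions are events unrelated to ascites. The article gives no indications for revision, and a revision could follow returning ascites.
- A reader might infer that TIPS in SMT adds many bleeding patients. Three of four list entries is not a share of patients. The recurrent-ascites indication requires at least three large-volume paracenteses, so the endpoint has normally already occurred. Patients enter with grade 3 ascites, or grade 2 with MELD ≥ 15, so many may have had a paracentesis before any bleed.
- Counting TIPS as treatment failure, or as a competing event, is a recognised strategy. The table entry may be a deliberate composite choice.

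The prose is consistent wherever it defines the endpoint, and only two table cells depart from it. This limits the consequence but does not remove the contradiction.

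**Conclusion.** The contradiction is real and confined to two cells. Table 4 has an undefined entry for TIPS implantation and revision, and its event half conflicts with Estimand 2 and the analysis text. It would be too strong to say that Table 4 definitely counts these procedures as events, or that the sponsor means to count the index TIPS. The entry is ambiguous, and the literal reading only shows why it must be resolved.

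The direction follows from the design: TIPS in SMT before any paracentesis lowers the hazard ratio, and revision before any paracentesis raises it. The size does not. The range of 0.36 to 0.62 against 0.40 rests wholly on assumed constant hazards, and with both rows counted the change can be as small as 0.40 to 0.41. The primary endpoint, the 57 events and the sample size are unaffected. The point is worth correcting because it can change a tested secondary result.

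**What to change.** Make Table 4 and Estimand 2 agree before outcome data are examined.

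The change that keeps the stated endpoint is *Ignore* in both TIPS cells of the paracentesis column, plus one line in Estimand 2 naming TIPS implantation and TIPS revision with that strategy. This matches Estimand 1. It also fits the treatment attribute that Estimand 2 takes over from Estimand 1, which compares randomised arms regardless of treatment changes. It sits well with {11a}, which already keeps a paracentesis done to facilitate TIPS out of the secondary endpoint.

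If a composite is intended, Estimand 2 must say so, state the handling of implantation and revision in each arm, and exclude the index TIPS explicitly. The event definition and competing-risk wording in {20a} should then follow.

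TIPS in the SMT group is already reported under safety in Table 2. TIPS revision is not listed there (only TIPS dysfunction), so a separate report of revisions would have to be added if wanted.

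The cost of keeping the stated endpoint is two cells and one line, with no new data.

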1. Patients ≥ 18 years and < 80 years. (Patients > 80 years independent of their physical constitution are excluded as they show higher complication rates and mortality after TIPS implantation) 2. Liver cirrhosis as documented by previous liver biopsy or by a combination of typical clinical, biochemical and sonographic features 3. Ascites as the first single decompensating event with grade 2 ascites and MELD ≥ 15 or grade 3 ascites [1] 4. Ability to understand the nature of the trial and the trial related procedures and to comply with them	1. Treatment refractory or recurrent ascites at the time of study inclusion 2. Patients with concomitant variceal bleeding fulfilling the criteria for pre-emptive TIPS implantation (Child–Pugh class C < 14 points or Child–Pugh class B > 7 with active bleeding at initial endoscopy or hepatic venous pressure gradient [HVPG] > 20 mmHg at the time of bleeding) 3. Budd-Chiari syndrome 4. Portal vein thrombosis (PVT) 5. Spontaneous bacterial peritonitis (SBP) 6. Uncontrolled systemic infection (defined as an increase of > 20% if inflammatory parameters [C-reactive protein, procalcitonin, leukocytes] and/or sepsis as a reason for development of ascites 7. Cardiac cirrhosis (defined as the development of liver cirrhosis in a patient with cardiac heart failure due to primary cardiac disease) 8. Clinical significant cardiac disease (NYHA ≥ II) 9. Untreated valvular heart disease: middle to high-grade valve stenosis or insufficiency (applies to mitral, tricuspid, aortic and pulmonary valves) 10. Diastolic dysfunction grade III, stated by transthoracic echocardiogram (TTE) 11. Reduced left ventricular ejection fraction ≤ 50% 12. Pulmonary hypertension (mean pulmonary arterial pressure > 45 mmHg) 13. Bilirubin > 3 mg/dl 14. Obstructive cholestasis 15. Hepatorenal syndrome type AKI 16. Acute on chronic liver failure 17. Benign liver tumor e.g. cysts within the potential puncture tract 18. Patient after liver transplantation 19. Prior TIPS implantation 20. Ongoing and/or recurrent hepatic encephalopathy (grade ≥ II) 21. Active tumor disease including hepatocellular carcinoma defined as need for chemotherapy, radiation therapy, interventional or surgical treatment 22. New onset of antiviral treatment for chronic hepatitis B virus (HBV) infection within the last 3 months 23. Untreated chronic hepatitis C virus (HCV) infection 24. Life expectancy < 1 year 25. Pregnant or breastfeeding women 26. Patients without legal capacity who are unable to understand the nature, significance and consequences of the study or who are judged as non-compliant (e.g. due to active drug abuse, severe alcohol abuse) 27. Simultaneous participation in other interventional trials which could interfere with this trial; simultaneous participation in registry and diagnostic trials is allowed 28. Person who is in a relationship of dependence/employment with the sponsor or the investigator

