In patients with grade > 2 ascites, LVP will be performed according to current recommendations. Plasma volume expansion with albumin infusion will be performed following completion of LVP (albumin 8 g/l of ascites drained). If less than 5 l of ascites was drained, no plasma expansion is necessary [1].

The current Baveno VII guidelines make a strong recommendation for the use of non-selective beta-blockers (NSBB; preferred carvedilol or propranolol) for the prevention of decompensating events and therefore, this will be a common co-medication in the SMT group. NSBB should be stopped in case of acute kidney injury (AKI) and persistently systolic blood pressure < 90 mmHg or mean arterial pressure < 65 mmHg. After blood pressure returns to normal and AKI is resolved, NSBB can be restarted [7].

In case of development of overt hepatic encephalopathy, treatment will be started incorporating lactulose (10 ml twice or more daily as necessary) and/or rifaximin 550 mg twice daily [17].

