### Sample size {14}

Sample size calculation is based on the primary endpoint transplantation-free survival (TFS), defined as time from randomisation to liver transplantation or death. It is assumed that the TFS probability of patients in the control group (SMT) is approximately 66% after one year. With an assumed TFS rate of approximately 82% in the TIPS group, this corresponds to a hazard ratio of 0.48 of the TIPS group compared to the control group (SMT group). The assumption is based on the study by Bureau et al. that analysed 62 patients. The one-year rate of TFS in the TIPS group was 93% (95%CI, 82%–100%) [12]. The TFS probability of the SMT group was assumed according to data from patients with first decompensation with ascites in the INCA trial (unpublished data [24] and, the data provided by Balcar et al. that report1-year TFS in patients with LVP [14]. The effect of TIPS implantation will be assessed by a test at two-sided significance level of 5% and by estimation of the hazard ratio with corresponding asymptotic two-sided 95% confidence interval. The null hypothesis is rejected if the confidence interval does not contain one. Under the above assumptions, the study is planned to detect a difference between the experimental intervention (TIPS group) and the control group (SMT group) with a power of 80%, which requires a total number of 57 events to be observed. The required number of patients to be randomised to observe this amount of events depends on the length of follow-up. With a recruitment period of three years, an additional follow-up period after the end of recruitment of two years, it can be safely assumed that a sufficient number of events will have been observed by the end of the trial if 116 patients are available for analysis (software used, e.g. n Query Advisor 8.3). Furthermore, the exponential drop-out rate is assumed to be 0.01. Therefore, 134 patients will be randomised. Before the end of the planned recruitment phase, a blinded assessment of the TFS rate (both treatments combined) will be performed. If the TFS rate appears to be higher than anticipated, the recruitment phase will be extended, and the required number of patients will be calculated anew under the amended assumptions. Irrespective of this sample size amendment, the analysis will be conducted after the observation of 57 events as planned, so no alpha adjustment is necessary.

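### Baseline ascites grade defines the two entry routes but is neither a stratum nor a Cox covariate; the plan stays valid but may lose precision, mainly for time to paracentesis

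*Protocol article*

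**What the plan says.** All places are in the protocol article.

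- **Eligibility criteria {10}, Table 1.** The third inclusion criterion sets two routes of entry: "Ascites as the first single decompensating event with grade 2 ascites and MELD ≥ 15 or grade 3 ascites". A MELD threshold applies to grade 2 only.
- **Sequence generation {16a}.** Site is the only stratification factor: "Randomisation will be performed, stratified by site, in blocks of variable length".
- **Statistical methods {20a}.** The same sentence fixes the covariates of the TFS model and of the paracentesis model: "The regression model will include treatment and study site as independent variables, as well as baseline bilirubin, creatinine and age". For SF-36 and CLDQ, the same section adjusts for the baseline value of the subscale being analysed.
- **Explanation for the choice of comparators {6b}.** Ascites grade is linked to drainage: "In patients with grade > 2 ascites, LVP will be performed according to current recommendations". The footnote to Table 2 classifies ascites with need for paracentesis on the same three-grade scale and adds symptoms as a trigger.
- **Background and rationale {6a}.** Both routes are described as high risk. No hazard ratio between them is given.

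**The concern.** Grade 3 versus grade 2 with MELD ≥ 15 is one binary variable, and eligibility cannot be confirmed without it. For time to paracentesis it is close to a baseline measure of the outcome itself. Bilirubin, creatinine and age do not measure how much ascites a patient has. The plan adjusts quality of life for its own baseline value but does not do the same for ascites.

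If grade is prognostic given the other covariates, leaving it out of a Cox model moves the estimated treatment HR towards 1 and lowers power. A chance difference in grade between the arms is also left unadjusted. What is at stake is precision, chiefly for a secondary endpoint, and not the validity of either test.

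**Working it through.** **1. The plan's own figure.** Sample size {14} assumes that the "TFS probability of patients in the control group (SMT) is approximately 66% after one year", and continues: "With an assumed TFS rate of approximately 82% in the TIPS group, this corresponds to a hazard ratio of 0.48". It aims to detect this difference "with a power of 80%, which requires a total number of 57 events to be observed", at a two-sided 5% level.

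- HR = ln 0.82 / ln 0.66 = 0.4776, stated as 0.48.
- Schoenfeld events = 4(1.960 + 0.842)² / (ln HR)². This gives 57.5 at 0.4776 and 58.3 at 0.48.
- Power at 57 events = Φ(√57 · |ln HR| / 2 − 1.960). This gives 79.7% at 0.4776 and 79.1% at 0.48.

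The 57 events are therefore reproduced to within rounding. The calculation claims no gain from covariates, so the omission does not contradict it.

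**2. Cost of one more parameter.** With about 10 sites, the planned model has 1 (treatment) + 9 (site) + 3 (bilirubin, creatinine, age) = 13 parameters. Grade makes 14.

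**3. Gain from adding grade.** There is no simple closed form, so trials were simulated and each was analysed with and without grade (3,000 trials per scenario). From the protocol: 134 patients, 10 sites, 3-year accrual, drop-out 0.01 (taken as per year) and, for TFS, analysis at 57 events. Assumed, because the protocol gives no values: a grade 3 share of 50% or 75%, and an HR of 1 to 3 for grade 3 versus grade 2. Also assumed for paracentesis: treatment HR 0.60, 40% event-free at one year under standard medical treatment, and a competing hazard of 0.3 per year, which yields about 87 to 89 events.

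Time to paracentesis, power without → with grade:

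| Assumed grade HR | Share 50% | Gain (points) | Share 75% | Gain (points) |
|---|---|---|---|---|
| 1.0 | 66.8 → 66.7% | −0.1 | 67.3 → 67.3% | 0.0 |
| 1.5 | 66.3 → 66.9% | 0.6 | 65.9 → 66.9% | 1.1 |
| 2.0 | 64.1 → 67.3% | 3.2 | 63.7 → 66.6% | 2.8 |
| 3.0 | 56.3 → 67.3% | 11.0 | 57.7 → 65.9% | 8.3 |

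TFS, power without → with grade:

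| Assumed grade HR | Share 50% | Gain (points) | Share 75% | Gain (points) |
|---|---|---|---|---|
| 1.0 | 78.8 → 78.9% | 0.0 | 79.6 → 79.1% | −0.6 |
| 1.5 | 78.9 → 79.4% | 0.5 | 75.8 → 77.1% | 1.3 |
| 2.0 | 76.2 → 78.3% | 2.1 | 77.4 → 78.0% | 0.6 |
| 3.0 | 71.8 → 77.9% | 6.1 | 74.8 → 78.7% | 3.9 |

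Gains come from unrounded figures. Their simulation standard errors are about 0.3 to 0.75 points, so differences below 1 point are mostly noise.

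**4. TFS with the entry rule built in.** Grade 2 patients were admitted only with MELD ≥ 15. Further assumptions were an HR of 1.11 per MELD point, bilirubin and creatinine acting as noisy proxies for MELD, and a resulting grade 3 share of 76%. At grade HRs (given MELD) of 1, 1.5, 2 and 3, the gains are −0.1, 0.1, 1.2 and 3.3 points. At 1.5 the two routes carry equal mean hazard (ratio 1.0): the MELD requirement for grade 2 cancels the grade contrast.

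**The case against.** The plan fixes a covariate set in advance and adjusts for its only stratification factor. Leaving out one more candidate breaks no rule, leaves type I error intact and contradicts nothing in the sample size. That stands.

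A reader might infer that both Cox models certainly lose power. The documents do not support this. They give no prognostic effect of grade among enrolled patients, they call both routes high risk, and the MELD threshold for grade 2 offsets the contrast for TFS.

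A reader might also infer that the protocol makes grade at entry determine later drainage. It does not. The large-volume paracentesis rule concerns ascites present at the time, and symptoms are a further trigger. Table 3 allows a paracentesis at screening, and a paracentesis before TIPS is expressly not counted as an endpoint under Intervention description {11a}. Either could weaken the link between grade at entry and the first counted paracentesis. The link need not vanish, but its strength is unknown.

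Finally, the movement of the HR towards 1 might be read as bias. Much of it reflects the fact that adjusted and unadjusted hazard ratios are different quantities, and a chance imbalance in grade is already covered by the confidence interval. The argument for adjustment is therefore one of efficiency. What survives is that the covariate list contains no measure of ascites load for an ascites endpoint, and that including one costs almost nothing.

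**Conclusion.** The point holds as an efficiency recommendation, mainly for the secondary endpoint. For time to paracentesis, omitting grade may cost about 1 point of power at a grade HR of 1.5, about 3 points at 2 and 8 to 11 points at 3. The loss could be smaller if ascites is drained at screening or before TIPS. For TFS the likely loss is about 0 to 2 points at a grade HR of 2 or less, and 3 to 6 points only near 3. If grade is not prognostic, adding it costs under 1 point in either model.

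The grade share, the grade HR, the MELD effect and all paracentesis rates are assumptions, so these sizes are conditional and are not estimates for this trial. The protocol states no power target for the paracentesis endpoint. The validity of both tests and the 57 events are unaffected.

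**What to change.** By amendment, before the data are analysed, add baseline ascites grade (grade 3 versus grade 2) as one binary covariate to the Cox model for time to paracentesis. Adding it to the TFS model is optional. Leave randomisation and the 57 events unchanged. Because the trial is open-label, the earlier this is fixed the better: a covariate added after an imbalance has been seen would look data-driven.

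The cost is one sentence and one extra parameter in each model it enters. No new assessment is needed, since grade is part of the inclusion criteria. It is worth checking that the eCRF stores the grade itself and not only that the criterion was met.
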